### Trial design {8}

This is a single-site, subjects-blinded, prospective parallel group and randomized controlled trial that conforms to the Standard Protocol Items: Recommendations for Interventional Trials (SPIRIT) 2013 Checklist [33] and standards for Reporting Interventions in Clinical Trial of Acupuncture [34] guidelines for Acupuncture studies. A total of 116 subjects will be included and randomly assigned to the acupuncture group and the sham acupuncture group in a 1:1 allocation radio. The flowchart of the study process is detailed in Fig. 1.

**Fig. 1 Fig1:**
[figure not shown]
Flowchart of this study

## Methods: participants, interventions, and outcomes

### Study setting {9}

All eligible participants will be accepting the trial in the department of ultrasound in medicine of Shanghai Municipal Hospital of Traditional Chinese Medicine, Shanghai, China.

### Eligibility criteria {10}

Inclusion criteria are as follows: male or female aged 18 to 35 who (1) have a body mass index (BMI) greater than 18.5 and less than 26 and (2) sign the informed consent as a subject voluntarily.

Exclusion criteria are as follows: (1) those who have large or small traumatic injury, skin ulcer, and other skin defects at ST36; (2) participants whose digestive system is found to have an organic lesion after ultrasonic examination; (3) participants with severe primary diseases of cardiovascular, pulmonary, hepatic, renal, and hematopoietic system or severe mental disorder; (4) participants who have been recently taking psychotropic drugs that affect digestion; (5) participants who cannot cooperate with researcher or are unwilling to accept acupuncture intervention; (6) participants who have participated in any other clinical trials in the past 3 months; and (7) participants who are considered inappropriate to be included in this trial by researchers.

### Who will take informed consent? {26a}

All participants will be recruited by advertising in WeChat groups and around universities in Shanghai, China. People who are interested in participating can contact the researcher by calling or adding the WeChat ID, and they will be subsequently evaluated according to the inclusion and exclusion criteria. We guarantee that all participants will be fully informed and understand in detail about the potential benefits and risks of the trial before they sign the informed consent.

### Additional consent provisions for collection and use of participant data and biological specimens {26b}

Not applicable, this trial does not have biological specimens.

## Interventions

### Explanation for the choice of comparators {6b}

In order to comply with the proposed objectives and verify whether depth and intensity of acupuncture will affect the motility of gastric antrum, we take the intervention of shallow acupuncture at ST36 as a way of contrast to distinguish from routine acupuncture. The sensations generated by shallow acupuncture are very slight but is similar to the feeling of true acupuncture. Furthermore, to a great extent, it ensures that the participants cannot distinguish the group distribution in appearance, which is beneficial to blind method implementation.

### Intervention description {11a}

All participants are asked to abstain from eating for at least 2 h before the trial. Participants in both groups will receive acupuncture on the right-sided ST36. A thermal infrared imager detects the thermal infrared spectrum of the gastric area skin and observes the antral contraction by ultrasonography.

#### Acupuncture group

Participants will take the supine position while wearing an eye-patch. The right calf and abdomen will be uncovered sufficiently to expose the lower border of the right patella and the space between the navel and xiphoid process respectively. The infrared imaging device will be used to measure the infrared thermal spectrum for 10 min at a lens distance of 1 m from the subject’s abdomen. Subsequently, sagittal scanning will be performed with an abdominal probe placed slightly to the right of the inferior of border of the xiphoid process. The left lobe of the liver, the lower pancreas, the abdominal aorta, and the superior mesenteric artery will be used as anatomical reference points to locate the gastric antrum. From here, the frequency of gastric antrum contraction will be recorded for 10 min continuously.

After sterilizing the skin, ST36 will be punctured at the insertion point under the guidance of ultrasonography until the needle tip reaches the crural interosseous membrane. A qualified and experienced acupuncturist will perform needle manipulation including lifting, thrusting and rotating to obtain the appropriate needling sensations (*deqi* sensation). Then, the researchers will record the frequency of antral contraction for 10 min with the ultrasonic probes and conduct needle manipulation in the 5th minute. After wiping the ultrasound gel off the skin until it thoroughly dried, the researchers will collect infrared thermal spectrum data from the abdomen.

#### Sham acupuncture group

Participants in the sham acupuncture group will be punctured at ST36 with the needle tip reaching no deeper than the superficial fascia and without any needle manipulations. The remaining procedures and recording details are the same as those of the acupuncture group.

### Criteria for discontinuing or modifying allocated interventions {11b}

The sonographer of this study will perform an ultrasound examination of the stomach before the trial to make sure there are no pathologic changes in the stomach. The trial will be discontinued if one of the following situations occurs: a large amount of gas in the gastrointestinal tract that affected the ultrasonic observation, which can result in collecting and analyzing data difficultly, and participants who have acupuncture-related serious adverse reactions during the experiment or failure to complete the study for any other reasons. We will record the details in the report for the early termination of the study.

### Strategies to improve adherence to interventions {11c}

At the beginning of the trial, participants will be informed of the experiment procedure again. They can report their personal feelings at any time during the study, and we will give corresponding feedback as appropriate to increase the interactivity and then improve adherence to interventions.

### Relevant concomitant care permitted or prohibited during the trial {11d}

Participants will not be allowed to eating or drinking during the entire study. In order to avoid the influence of other factors on body temperature, participants should also be prohibited from leaving the bed for free movement.

### Provisions for post-trial care {30}

At the end of the study, we will provide certain amount of subsidy to each subject. If the adverse events occur during the trial that related to the intervention after the expert committee confirms, the responsible department will provide corresponding economic compensation, psychological comfort, and treatment modalities. Before the trial, the participants will be informed that participation in this study is voluntary, they can withdraw from the study at any time for any reasons, and their benefits will not be affected.

## Outcomes {12}

We will assess the function of gastric antrum contraction by visualizing the antral area, frequency and amplitude during the contraction of gastric antrum and assess this data through the antral motility index [35]. Data collected from the ultrasound will be measured by means of recording and playback.

### Primary outcome

Antral contraction frequency (ACF) is the primary outcome of this study. The ultrasound probe will be placed vertically to simultaneously obtain the image of gastric antrum, superior mesenteric artery, abdominal aorta, and left lobe of the liver. ACF will be recorded for 10 min before and after the continuous needling. Frequency of antral contractions = number of contractions per 10-min period.

### Secondary outcomes

#### Antral contraction amplitude (ACA)

Antral contraction amplitude (ACA) is an average value calculated as follows: amplitude (%) = (antral area at relaxation − antral area at contraction)/antral area at relaxation × 100. The minimum and maximum cross-sectional areas of the antrum will be measured during contractions and relaxations a minimum of 4 times to calculate the amplitude of antral contractions. The antral area will be measured by the Bolondi method [36] which takes the length diameter (*L*) and the width diameter (*W*) of sagittal plane of the antral as parameters for the computational formula (*A* = *L* × *W* × *π*/4).

#### Antral motility index (AMI)

The antral motility index (AMI) is represented as the antral contraction frequency (ACF) multiplied by the antral contraction amplitude (ACA).

#### Infrared thermal spectrum

The infrared thermal spectrum will be measured for 10 min before and after needling by FOTRIC 225 medical infrared imager. We will take the value of the highest temperature within 10 min as the final result of skin temperature in the abdominal region.

#### Ultrasonic anatomical diagram of ST36

A high-frequency ultrasound probe (18 MHz) will be used to conduct spatial positioning at the acupoint before acupuncture. The vertical distance between important structures (anterior tibial artery, deep peroneal nerve and crural interosseous membrane) and the skin will also be measured. The probe will also be used to collect a static and dynamic ultrasonogram of the *deqi* sensations.

#### Clinical evaluation scale for subject sense of acupuncture

This scale is the Chinese version of the Massachusetts General Hospital Acupuncture Sensation Scale (MASS) which has previously been shown to be accurate and reliable [37]. This scale is composed of a main scale and 2 supplementary scales for measuring the spread of the acupuncture sensations and anxiety. At the end of the trial, participants will be asked to fill in the C-MASS form (see additional file 1) to evaluate the intensity of 12 acupuncture sensations on a 0–10-cm VAS, where 0 represents “none” and 10 represents “intolerably strong sensation.” The participants can assess any other sensations by an additional blank row included at the end of the form. The MASS index will then be calculated.

#### Clinical evaluation scale for acupuncturist sense of acupuncture

This scale (see additional file 1) is aimed at the evaluation of the acupuncturist’s feeling of sensations conducted through the needle tip. This data will be collected at the end of the experiment and contains 2 aspects: property and corresponding layer of needling sensations. This scale has reliable content validity and contains 6 sensory items from the experts intentional survey [38].

### Participant timeline {13}

The timing of intervention and data collection is detailed in Fig. 2.

**Fig. 2 Fig2:**
[figure not shown]
The recommended SPIRIT figure with the participant timeline. 0_=_ baseline_=_ pre-acupuncture; *t*_*1* =_ during acupuncture; *t*_*2*_ = post-acupuncture; ACF, antral contraction frequency; ACA, antral contraction amplitude; AMI, antral movement index; C-MASS, Chinese-Massachusetts General Hospital Acupuncture Sensation Scale; ANSE scale, acupuncturist needling sensations evaluation scale

### Sample size {14}

The sample size was estimated using the Power Analysis and Sample Size (PASS version 15) software. According to our pilot trial, we anticipate that the change in the frequency of antral contraction will be more pronounced in the acupuncture group than in the sham acupuncture group and that we will detect a difference of 30% between effective rates in the 2 groups (70% in the acupuncture group compared with 40% in the sham acupuncture group). On the basis of a 2-sided alpha level of 0.05 and a power level of 90% with a 10% dropout rate, we calculated that our trial will require a sample of 116 participants (58 in each group).

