**Methods:**

This is a two-arm, single-blind, randomized, controlled trial. A total of 116 acupuncture-naïve healthy subjects will be randomly allocated to the acupuncture group or sham acupuncture group in a 1:1 ratio. Participants in the acupuncture group will receive manual acupuncture at Zusanli (ST36) with the needling depth at crural interosseous membrane. Those in the sham acupuncture group will be given penetrating needling depth at the superficial fascia layer. The primary outcome will be the changes in antral contraction frequency (ACF) before and after acupuncture. The secondary outcomes will be the changes in the thermal infrared spectrum of gastric area skin, the antral contraction amplitude (ACA), the antral movement index (AMI), and the scores on the Chinese version of Massachusetts General Hospital Acupuncture Sensation Scale (C-MASS). The adverse events will be evaluated and recorded in detail.

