## Statistical methods

### Statistical methods for primary and secondary outcomes {20a}

Data analyses will be performed with the statistical software SPSS23.0 by an independent statistician. The analysis will include an intention-to-treat(ITT) analysis, including data for all participants who dropped out of the trial. Descriptive statistical analysis will be used for all demographic and clinical characteristics of subjects such as sex, age, and weight. We will validate the homogeneity of demographic characteristics and examine the variables between the 2 groups. The mean ± standard deviation will be used for description of the continuous variables. Qualitative data will be expressed in terms of frequency and percentage.  Student's t-test will be used to compare the measurement data between the 2 groups. Rank-sum test is used for ranked data, while the chi-squared test is adopted to analyze categorical data. The significance level used for statistical analysis with 2-tailed testing will be 5%.

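### The 90% power is calculated for an undefined effective rate, not for the primary outcome (change in antral contraction frequency), so it does not apply to the primary analysis

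*Protocol article*

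**What the plan says.** **Basis of the sample size.** Sample size {14} cites a pilot, expects a larger change in contraction frequency with acupuncture, and then turns to proportions: "we will detect a difference of 30% between effective rates in the 2 groups", namely "70% in the acupuncture group compared with 40% in the sham acupuncture group". The total of 116 (58 per group) is derived "On the basis of a 2-sided alpha level of 0.05 and a power level of 90% with a 10% dropout rate".

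**Primary outcome.** The abstract says: "The primary outcome will be the changes in antral contraction frequency (ACF) before and after acupuncture". The Primary outcome section gives the scale: "Frequency of antral contractions = number of contractions per 10-min period".

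**Analysis.** Statistical methods {20a} assigns tests by type of data. Student's "t-test will be used to compare the measurement data between the 2 groups"; categorical data go to chi-squared and ranked data to a rank-sum test. ACF is not named beside any test. Analysis is by intention to treat and includes dropouts, and section {20c} replaces missing values with the participant's baseline value.

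**What is absent from the article.** No section states when a participant counts as effective. No effective or responder rate appears under Outcomes {12}. No mean change, mean difference or SD for ACF is given.

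**The concern.** The size was derived for one quantity, and the trial's primary outcome is another. The power of a two-proportion comparison is fixed by the two rates. The power of a t-test on change in ACF is fixed by the mean difference relative to its SD. One cannot be read from the other without a threshold and a distribution, and the article supplies neither.

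The 90% is the figure by which readers will judge the choice of 116 healthy volunteers and interpret a null result. If the t-test shows no difference, the article as written invites the statement that a trial with 90% power found nothing, and that power was never worked out for the t-test. This is more than condensation for a journal: the article does give its sample-size basis, and that basis does not match the primary outcome it states.

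**Working it through.** **1. Reproduce the stated figure.** Inputs from Sample size {14}: p₁ = 0.70, p₂ = 0.40, two-sided α = 0.05 (z = 1.960), power 90% (z = 1.282), dropout 10%.

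Unpooled two-proportion formula:

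n = [p₁(1 − p₁) + p₂(1 − p₂)] × (1.960 + 1.282)² / (p₁ − p₂)²
= (0.21 + 0.24) × 10.507 / 0.09 = 52.54 per arm.

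Dropout allowance: 52.54 × 1.1 = 57.8, rounded up to 58 per arm, 116 in total. This matches the plan exactly.

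Exact power of Pearson's chi-squared test for 70% v 40% is 89.5% at 52 per arm and 91.1% at 58 per arm. So the 90% is a fair description of the binary comparison.

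**2. Compare the endpoint sized with the endpoint analysed.**

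| | Sample size {14} | Outcomes {12} and Statistical methods {20a} |
|---|---|---|
| Quantity | proportion effective | change in ACF, contractions per 10 min |
| Definition | none in the article | given |
| Listed as an outcome | no | yes, primary |
| Test | comparison of two proportions | t-test, by the rule for measurement data |
| Planning values | 70% v 40% | no mean difference or SD |

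**3. What 116 gives for the t-test.** Two-sided 5%, noncentral t. The standardised difference d (mean difference in ACF change divided by its SD) is an assumption, because the article gives none.

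| d | Power, 58 per arm | Power, 52 per arm |
|---|---|---|
| 0.3 | 36% | 33% |
| 0.4 | 57% | 52% |
| 0.5 | 76% | 71% |
| 0.6 | 89% | 86% |
| 0.7 | 96% | 94% |
| 0.8 | 99% | 98% |

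90% power is reached at d = 0.607 with 58 per arm and d = 0.642 with 52 per arm. The 58 is the number analysed under the intention-to-treat rule. The 52 is 58 × 0.9 = 52.2, the number with complete data if 10% drop out.

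**4. Effect of baseline substitution.** Replacing a missing post-needling value with baseline sets that participant's change to zero. Suppose this happens to 10% of each arm (assumption). The mean difference Δ shrinks to 0.9Δ. Within an arm with mean change μ and SD σ, the variance becomes 0.9σ² + 0.09μ². If μ is small beside σ, the SD is √0.9 σ = 0.949σ, so d falls to (0.9 / 0.949)d = 0.949d. The true difference needed with 58 per arm is then about 0.607 / 0.949 = 0.64 SD, and more if the mean changes are not small. Substitution thus cancels the apparent gain from analysing 58 rather than 52.

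**5. The one route from 70/40 to the t-test.** Assume that effective means exceeding a single cut-off of a normally distributed change in ACF, with equal SDs. Then d = z(0.70) − z(0.40) = 0.524 + 0.253 = 0.78, and t-test power at 52 per arm is about 97.5%. This rests wholly on an assumption that the article does not state, but it points towards adequate power.

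**The case against.** **The rates obviously refer to ACF.** The sentence in Sample size {14} does tie them to change in contraction frequency, so a responder split of that change is the natural reading. That stands, but it gives no cut-off, and the rate is still not an outcome.

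**Chi-squared is in the plan, and ACF is not named beside the t-test.** Both are true. The t-test link is inferred from ACF being a count, that is, measurement data. The chi-squared sentence is generic, and no listed outcome is an effective rate for it to test.

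**The full protocol may define the threshold.** It may, and the article's silence on a cut-off would not be a fault by itself. It would not make a power figure for two proportions apply to a t-test on a count.

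**Stronger readings that the document does not support.**
- A reader might infer that the trial is underpowered. Nothing shows this. The low powers in the table come from assumed values of d, and the only mapping from the plan's own rates gives about 97.5%.
- A reader might infer that 116 is miscalculated, because other formulas or dividing by 0.9 give a slightly larger total. The article does not say how dropout was applied, one ordinary route gives 116 exactly, and exact chi-squared power lies within about one percentage point of 90% at either 52 or 58 per arm.
- A reader might infer an intention to choose a cut-off after seeing the data. The article plans no additional analyses and blinds its statisticians and data analysts. An unfixed threshold is a loose end, not evidence of intent.

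**Conclusion.** The point holds in a limited form. The 116 participants and 90% power are correct for comparing 70% with 40%, but that endpoint is neither defined nor listed in the article, and the primary outcome is a change in a count. Power for the primary analysis is therefore not established. What can be said is that 90% power needs a difference of about 0.61 SD with 58 per arm analysed, or about 0.64 SD with 52 complete per arm or once baseline substitution in 10% of each arm is allowed for.

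This rests on two things: that the t-test is the test for change in ACF, which follows from the rule for measurement data, and that no SD or mean difference for ACF appears in the article. Whether the trial has more or less than 90% power for its primary comparison cannot be decided from the document.

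**What to change.** Keep n = 116 and rewrite Sample size {14} for the change in ACF.

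1. State the pilot mean change and SD of ACF in each group, and from them the power of the planned t-test at two-sided 5%, or the difference detectable with 90% power, in contractions per 10 minutes. The guide values are 0.61 SD (58 per arm analysed) and 0.64 SD (52 per arm complete), each multiplied by the pilot SD.
2. Say which number is assumed in the analysis, and allow for the dilution from baseline substitution, so that the section agrees with {20a} and {20c}.
3. Either delete the 70% and 40% effective rates, or fix the ACF-change threshold before unblinding and list the effective rate as a secondary outcome tested by chi-squared.

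The cost is one rewritten paragraph using pilot data that the article says exist; the restatement itself needs no additional participants. The downside is that the restated figure may look less favourable: if the pilot difference is below about 0.6 SD, the section must report power under 90%.

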### Methods in analysis to handle protocol non-adherence and any statistical methods to handle missing data {20c}

All data in this study will be analyzed according to the principle of ITT to reduce deviation, including the subjects who withdraw from the study during the study period. The missing data will be substituted into the subjects’ baseline data for final data analysis.

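### The 10% dropout allowance treats dropouts as leaving the analysis, but the plan keeps them at baseline values; on that rule 116 participants give about 84% power for 70% v 40%, not 90%

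*Protocol article*

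**What the plan says.** Protocol article, Sample size {14}: the calculation was done in PASS 15 for a comparison of effective rates, "70% in the acupuncture group compared with 40% in the sham acupuncture group". The operating characteristics are given as "On the basis of a 2-sided alpha level of 0.05 and a power level of 90% with a 10% dropout rate", and the result is stated as "we calculated that our trial will require a sample of 116 participants (58 in each group"). The section links the effective rate to the change in antral contraction frequency but does not say what change makes a participant effective. It names neither the test nor the variance form used.

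Statistical methods {20a}: the intention-to-treat analysis includes participants who dropped out, and "the chi-squared test is adopted to analyze categorical data".

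Missing data {20c}: the intention-to-treat principle is applied to all data, "including the subjects who withdraw from the study during the study period", and missing values are replaced by the participant's own baseline value.

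**The concern.** A dropout allowance and a missing-data rule have to describe the same analysis. Adding participants for expected dropout protects power only if those who drop out are left out and the remainder still show 70% v 40%. Here they are kept, with a post-needling value set equal to baseline. For an outcome based on change, that is a change of zero, which on the natural reading cannot be a response. Both rates then shrink in proportion to dropout, and so does the difference between them. Having all 58 per arm in the denominator does not make up for the smaller difference.

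At stake is whether the stated 90% describes the planned analysis. If it does not, a null result would be read against a power that the trial did not have.

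**Working it through.** **Inputs.** From Sample size {14}: rates 0.70 and 0.40, two-sided alpha 0.05 (z = 1.960), power 90% (z = 1.282), dropout 10%, 58 per arm. From the abstract's Methods: 1:1 allocation. From {20a} and {20c}: dropouts retained, baseline value substituted.

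**Step 1. Reproduce 116.** Unpooled two-proportion formula:

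n = (1.960 + 1.282)² × (0.70 × 0.30 + 0.40 × 0.60) / 0.30² = 10.507 × 0.45 / 0.09 = 52.54 per arm.

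52.54 × 1.10 = 57.8, so 58 per arm and 116 in total. The stated figure is reproduced exactly. Rounding to 53 and dividing by 0.90 gives 58.9, so 59 per arm and 118 in total, which is one more per arm.

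**Step 2. Power if dropouts are excluded.** 58 × 0.90 = 52.2, so 52 evaluable per arm at 70% v 40%:

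| Method | Power |
|---|---|
| Pooled normal approximation | 87.9% |
| Unpooled normal approximation | 89.7% |
| Exact binomial enumeration, chi-squared test without continuity correction | 89.5% |

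**Step 3. Power under the plan's rule.** Assume that 10% in each arm lack post-needling data, independently of response, and that zero change is not effective:

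- acupuncture: 0.70 × 0.90 = 0.63
- sham: 0.40 × 0.90 = 0.36
- difference: 0.27 instead of 0.30, with 58 per arm in the denominator

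Unpooled: 0.27 / √[(0.63 × 0.37 + 0.36 × 0.64) / 58] = 0.27 / √(0.4635 / 58) = 3.020; 3.020 − 1.960 = 1.060; power 85.6%.

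Pooled (mean rate 0.495): [0.27 × √58 − 1.960 × √(2 × 0.495 × 0.505)] / √0.4635 = 0.985; power 83.8%.

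Exact enumeration, chi-squared test without continuity correction: 84.0%.

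**Step 4. Sensitivity to the dropout rate.** 58 per arm throughout, dropouts counted as not effective:

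| Dropout per arm | Rates | Pooled | Exact chi-squared | Unpooled |
|---|---|---|---|---|
| 0% | 70% v 40% | 91.2% | 91.1% | 92.6% |
| 2% | 68.6% v 39.2% | 89.8% | 89.8% | 91.4% |
| 5% | 66.5% v 38.0% | 87.7% | 87.8% | 89.4% |
| 10% | 63% v 36% | 83.8% | 84.0% | 85.6% |

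At the protocol's own 10%, all three methods fall at least 4 points short of 90%.

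**The case against.** The strongest reply is that the 84% rests on conditions the protocol does not state. Effective is undefined, so scoring zero change as a non-response is an inference. The figure also needs every dropout to have a usable baseline recording and no post-needling recording, with equal loss in both arms. This is a single sitting with no follow-up, so actual loss may be below 10%. One named reason for stopping is gas that obscures the ultrasound view, and such a participant may have no baseline value to substitute. Finally, the primary outcome is a contraction count, for which {20a} would point to a t-test, so the responder comparison may not be the primary analysis at all.

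Most of this stands as a call for a stated assumption and a range, and Step 4 gives one. It does not remove the mismatch. The 10% is the protocol's own figure, and the sample size section itself ties the effective rate to change in contraction frequency. Which analysis is primary is a separate question; the point here is whether the stated power holds for the comparison on which the sample size was based.

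A reader might go further and infer that 116 is too small even with dropouts excluded, because the pooled formula gives 56 evaluable per arm and 56 / 0.90 = 62.2, so 63 per arm or 126 in total. The document does not support that. It does not name the pooled formula, the unpooled formula reproduces 116, and the exact power of the uncorrected chi-squared test at 52 per arm is 89.5%. At 56 per arm it is 89.6%, practically the same. Multiplying by 1.10 instead of dividing by 0.90 costs about one participant per arm, which is a remark and not an error of substance.

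**Conclusion.** The point holds as an inconsistency between the dropout allowance in {14} and the retention and substitution rules in {20a} and {20c}. Under those rules, 58 per arm give about 84% power for the 70% v 40% comparison at 10% dropout (84 to 86% across methods without continuity correction). The type II risk is therefore about 14 to 16% instead of 10%. At 5% dropout, power is about 88 to 89%.

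This assumes that zero change is not effective, that dropout is equal in the two arms and unrelated to response, and that dropouts have a baseline value but no post-needling value. It does not show that 116 was miscalculated: with dropouts excluded, the stated 90% is approximately right.

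**What to change.** Keep 116. In Sample size {14}, name the test and variance form used in the software, say whether zero change counts as not effective, and restate the power on the basis of the planned handling of dropouts. For example: with 58 per arm, power for 70% v 40% at a two-sided 5% level is about 84% if 10% per arm are retained at baseline values and counted as not effective, and about 90% only if dropouts are excluded.

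The cost is a sentence or so and a less favourable stated power. Recruitment, procedures and the missing-data rule need not change.
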